# Clinical efficacy of Tailin formulation combined with continuous low-dose antimicrobial therapy for recurrent urinary tract infection: study protocol for a multicenter, double-blind, randomized, controlled clinical trial

**DOI:** 10.1186/s13063-021-05830-4

**Published:** 2021-12-11

**Keywords:** Tailin formulation, Recurrent urinary tract infection (rUTI), Continuous low-dose antibiotic therapy (CLAT), Traditional Chinese medicine (TCM), Randomized controlled trial (RCT)

## Abstract

**Background:**

Given the increasing rates of antimicrobial resistance (AMR), recurrent urinary tract infection (rUTI) is becoming refractory more and more. Antibiotic prophylaxis including continuous low-dose antibiotic therapy (CLAT), is the common treatment for rUTI of the world. However, the presumably adverse reactions caused by CLAT alone should be paid more attention. Studies indicated that Chinese herbal medicine (CHM) might be an available treatment method for rUTI. Tailin formulation (TLF) is a herbal prescription developed for the treatment of rUTI in the 2000s in Shanghai Municipal Hospital of Traditional Chinese Medicine. Our previous studies have shown TLF could prevent urinary tract infection both in pyelonephritis (PN) rat model and in PN patients. Additionally, our published data demonstrated TLF is helpful to reduce the recurrence of rUTI and protect renal tubular function in clinic. In order to find a novel treating project for rUTI to increase the clinical curative effect, we thus try to combine TLF with CLAT to treat rUTI and design an optimized, pragmatically clinical trial to evaluate the efficacy and safety of this project.

**Methods/design:**

This is a multicenter, double-blind, randomized, controlled clinical trial. We will enroll 200 eligible patients diagnosed with uncomplicated rUTI and then divide them randomly into two groups with a 1:1 ratio: TLF + CLAT group and placebo + CLAT group. This trial consists of two stages, a 12-week period of treatment and a 12-week period of post-treatment follow-up, respectively. The primary outcome will be the recurrence rate at the 12th week of the follow-up period; the second outcomes will be the post-treatment changes in renal and liver function; furthermore, traditional Chinese medicine (TCM) symptoms, non-infection-related physical signs, and subjective symptoms will be scored, and the number of episodes of each subject will be also recorded; meanwhile, vital signs indicators and serious adverse events (SAEs) will be monitored throughout the trial.

**Discussion:**

This study will provide convictive research-derived data to evaluate clinical efficacy and safety of TLF combined with CLAT for rUTI, and provide an evidence-based recommendation for clinicians. Moreover, post-treatment changes in non-infection-related physical signs and subjective symptoms were included in the efficacy evaluation, which is important and more significant for assessing the clinical benefits for those rUTI patients.

**Trial registration:**

Chinese Clinical Trial Registry ChiCTR2100041914. Registered on 10 January 2021. Protocol date and version: September 12, 2020; version 1.

**Supplementary Information:**

The online version contains supplementary material available at 10.1186/s13063-021-05830-4.

## Background

RUTI in adults is defined as repeated urinary tract infection (UTI) with a frequency of 2 or more UTIs in the last 6 months or 3 or more UTIs in the last 12 months [1], which is a common clinical infectious disease, with particular presence in women. It is estimated that 2 in 5 of women will have at least one UTI during their life, and almost one third of them will have recurrence [2]. Antibiotic prophylaxis including continuous low-dose antibiotic therapy is the common treatment for rUTI of the world [3]. However, there are growing concerns about the presumably side effects, adverse reactions, and the increasing risk of bacterial resistance [4]. Given the increasing bacterial resistance, rUTI is becoming refractory more and more [5].

CHM has a recorded history of over 2000 years that may be used in the treatment of rUTI [6]. Previous studies indicated that CHM might be an available treatment method of rUTI for relieving acute UTIs and preventing recurrent episodes [7–9].

TLF is a herbal prescription developed for the treatment of rUTI in the 2000s [10] in the Shanghai Municipal Hospital of Traditional Chinese Medicine. In the past 17 years, our group focuses on the basic and clinical research of rUTI, including in vitro and in vivo, basic and clinical experiments [10–15]. In clinical trials, we find that TLF could effectively reduce the recurrence rate of chronic pyelonephritis (CPN) patients and protect their renal tubular function [10]. In animal experiments, we have built multiple rat models of UTI by Escherichia coli (*E. coli*) O_111_B_4_ successfully, including cystitis, acute pyelonephritis (APN), and CPN rat model, and their results suggested that TLF might effectively inhibit acute and chronic renal tubular and interstitial inflammation caused by *E. coli* retrograde infection, protect renal tubular function, and decrease renal tubular and interstitial fibrosis in rats [11–15].

With the aim to find a novel treating project for rUTI to increase the clinical curative effect, reduce the presumable side effects of CLAT used alone, and improve the clinical benefit for patients, we thus try to combine TLF with CLAT to treat rUTI and design this multicenter, double-blind, randomized, controlled clinical trial to achieve our goal.

## Methods/design

### Primary objective and study hypothesis

This clinical trial aims at obtaining convictive research-derived data to evaluate the efficiency and safety of TLF combined with CLAT for rUTI and improve the clinical benefit for patients. We hypothesize that TLF combined with CLAT will be effective and superior to CLAT alone for increasing the clinical curative effect, reducing the presumably side effects.

### Trial design

We designed a multicenter, double-blind, randomized, controlled clinical trial lasting 24 weeks, including a 12-week treatment period and 12-week follow-up. This trial was designed to comply with the *Declaration of Helsinki* [16] and the *Good Clinical Practice* (GCP) [17] (Fig. 1). The additional file 3 contains the SPIRIT 2013 Checklist.

**Fig. 1 Fig1:**
[figure not shown]
Study flow

### Sample size

The sample size will be calculated by PASS (version 15.0) and based on the effective rate of treatment. Group sample sizes of 91 in the treatment group and 91 in the control group achieve 90% power to detect a difference between the group proportions of 0.18. The proportion in the treatment group is assumed to be 0.91, and the proportion in the control group is 0.73 [18]. The significance level of the test is 0.025. With assuming attrition rate of 10%, a planned recruitment target of 200 patients will be set, 100 in each group.

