## Outcomes

### Primary efficacy outcome

The primary efficacy outcome will be the recurrence rate at the 12th week of the follow-up period.

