### Statistics of recurrence

Recurrence rate of UTI of each patient during the treatment until the end of the follow-up will be calculated separately and compared at the end of the trial.

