### Data analysis

Statistical analysis data set includes intention-to-treat (ITT) and per-protocol population. ITT will be applied to the full analysis set (FAS) consisting of all randomized subjects. Subjects who have received two or more weeks of treatment will be included in the per-protocol population. Both two sets will be analyzed at the end of this study. The reasons for excluding patients from the Per-Protocol Population should be recorded clear and documented prior to breaking blindness. Statistical analysis results of the two data set will be compared and analyzed after the trial completes.

Statistical analysis includes (1) baseline data analysis, (2) effectiveness analysis, and (3) security analysis. SPSS21.0 statistical analysis software will be used for statistical analysis. Two-sided test will be used for all statistical tests, and a *P* value less than 0.05 was considered statistically significant. Multiple imputation will be applied to missing data, and sensitivity analysis will be conducted to demonstrate the robustness of the results, when the high missing data proportions occur.

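### The stated 90% power is for an undefined effective rate (0.91 v 0.73) and is not shown to apply to the primary outcome, UTI recurrence

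*Protocol article*

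**What the plan says.** The Sample size section of the protocol article bases the calculation on one quantity: it is "based on the effective rate of treatment". The inputs follow: "The proportion in the treatment group is assumed to be 0.91" and "the proportion in the control group is 0.73", with a reference cited for them. With 91 patients per group the trial is said to "achieve 90% power to detect a difference between the group proportions of 0.18". On the level it says only "The significance level of the test is 0.025", without saying whether that is one-sided or two-sided. Allowing 10% attrition, the target is 200 patients, 100 per group.

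Under Primary efficacy outcome the article names something else: "The primary efficacy outcome will be the recurrence rate at the 12th week of the follow-up period". The Abstract agrees. Under Statistics of recurrence the window is longer: "Recurrence rate of UTI of each patient during the treatment until the end of the follow-up will be calculated separately".

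Under Data analysis, "Two-sided test will be used for all statistical tests", with significance at P below 0.05.

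**The concern.** The term effective rate appears only in the Sample size section. It is not defined there or elsewhere, and it is not among the primary or secondary outcomes. The nearest candidates are the four-level recovery grading in Table 3, built from symptom score, symptoms and signs, urine routine and culture, and the short-term and long-term cure rates that rest on it. Neither is called the effective rate, no level or combination of levels is labelled effective, and neither is stated to be equivalent to freedom from recurrence. Recurrence has its own definition under Relapse or reinfection and its own counting rule under Statistics of recurrence.

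Both the sizing quantity and the primary outcome are printed in the article and they differ, so this is not a detail left to a fuller protocol or an analysis plan. At stake is the planned assurance of detecting a stated effect on recurrence: a reader cannot tell what reduction the trial was designed to find, or with what probability.

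**Working it through.** **1. Reproduce the stated figure.** Inputs from the Sample size section: 0.91, 0.73, difference 0.18, power 90%, level 0.025. Taking the level as one-sided (the same critical value as two-sided 0.05), with unpooled variance:

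n = [p1(1 − p1) + p2(1 − p2)] × (1.960 + 1.282)² / d²

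= (0.0819 + 0.1971) × 10.507 / 0.0324 = 90.5, so 91 per group.

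This matches. The pooled-variance formula gives 94, and 89.2% power at 91. The arithmetic is sound for 0.91 v 0.73. Read as two-sided, 0.025 would need 107 (unpooled) or 111 (pooled), so the article's own 91 points to the one-sided reading.

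**2. Evaluable number.** 100 × 0.90 = 90 per group. (91 / 0.90 = 101.1, so 102 would be needed to keep 91; the gap is trivial.)

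**3. Power for recurrence.** The article gives no recurrence rates, so those below are assumptions, and recurrence is taken as the proportion of patients with at least one episode. With n = 90 per group, two-sided 0.05 and p̄ the mean of the two proportions:

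power = Φ{ [d√n − 1.960√(2p̄(1 − p̄))] / √[p1(1 − p1) + p2(1 − p2)] }

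*If effective means recurrence-free (27% v 9%):* (1.708 − 1.065) / 0.528 = 1.217, power 89%. This is a relative reduction of 18/27, or two thirds.

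*Worked example, 30% v 15%:* (1.423 − 1.157) / 0.581 = 0.457, power 68%.

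| Control recurrence | 30% relative reduction | 40% | 50% |
|---|---|---|---|
| 20% | 19% (v 14%) | 31% (v 12%) | 47% (v 10%) |
| 30% | 28% (v 21%) | 47% (v 18%) | 68% (v 15%) |
| 40% | 40% (v 28%) | 64% (v 24%) | 84% (v 20%) |
| 50% | 53% (v 35%) | 79% (v 30%) | 94% (v 25%) |

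The assumed treatment-group recurrence is in brackets. Power runs from 31% to 94% for reductions of 40–50%, and falls to 19% at the low end if a 30% reduction is admitted.

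**4. Difference detectable with 90% power.** Solving the same formula for d at n = 90:

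| Control recurrence | Detectable difference | Relative risk |
|---|---|---|
| 30% | 19 points | 0.36 |
| 40% | 22 points | 0.46 |
| 50% | 23 points | 0.54 |

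**The case against.** The strongest reply is that 0.91 and 0.73 come from a cited source that is not available here. If effective there means recurrence-free, the stated power carries over almost intact, at 89%. The article also ties its grading to infection in places: an acute UTI during treatment is marked as no recovery, and long-term cure is judged 12 weeks after medication ends, the time point of the primary outcome. This stands far enough that the favourable reading cannot be excluded. It does not close the gap, because the article never states that reading and never offers 27% and 9% as recurrence assumptions.

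A reader might go further the other way and infer that the effective rate cannot be the complement of recurrence, because patients enter in a non-acute state or in remission and so have no infection to recover from. The document does not support that. Table 3 grades symptom improvement, and every entrant must meet the TCM symptom criteria, so patients in remission can be graded. All that can be said is that equivalence is not stated.

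A reader might also pair the 0.025 level with the two-sided rule under Data analysis and infer a real loss of power. The article's 91 per group reproduces only with one-sided 0.025, which for a superiority comparison is the same as two-sided 0.05. This is unstated sidedness, not a sizing error.

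**Conclusion.** The point holds as a failure to link the sample size to the primary outcome. The calculation is correct for 0.91 v 0.73, but the 90% is not established for recurrence: the sizing quantity is undefined, it is not a listed outcome, and no recurrence assumption is given for either group. The figure survives, at about 89%, on one unstated reading. Otherwise power depends on rates the article does not give, from 31% to 94% over the 40–50% reductions examined. These figures rest on assumed recurrence rates, 90 evaluable patients per group, a comparison of proportions and two-sided 0.05.

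Two stronger conclusions might be drawn, and neither is supported. The trial is not shown to be underpowered, since some plausible scenarios reach or exceed 84%. Nor would a null result be uninterpretable, since a confidence interval for the difference in recurrence could still be read. What is missing is a declared target effect and the power to detect it.

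**What to change.** Keep 200 patients and rewrite the Sample size section:

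- First reconcile the recurrence window. The Primary efficacy outcome section refers to week 12 of follow-up, while Statistics of recurrence runs from treatment to the end of follow-up. No control rate can be stated until one window is fixed.
- State an assumed control recurrence proportion and a target reduction for that window, with support. Alternatively, if 0.91 and 0.73 are recurrence-free proportions, say so and support 27% and 9%.
- Report power, or the difference detectable with 90% power, at about 90 evaluable per group over a range of control rates.
- Remove the 90% claim for the undefined effective rate. Relabelling it as a secondary-outcome calculation is not open as the text stands, because the rate is not among the secondary outcomes.
- State the level as two-sided 0.05, which is equivalent to the one-sided 0.025 that yields 91 and matches the Data analysis section.

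The cost is rewording and a stated power that may be less favourable. No extra patients are needed for this change.

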### Screening and recruitment of participants

This study intends to enroll 200 cases mainly from the nephrology outpatient and inpatient departments, including 80 cases from Shanghai Municipal Hospital of Traditional Chinese Medicine, 60 cases from the Sixth People’s Hospital affiliated to Shanghai Jiaotong University, and 60 cases from Baoshan Hospital of Integrative Chinese and Western Medicine Affiliated to Shanghai University of Traditional Chinese Medicine. According to the inclusion and exclusion criteria set based on diagnostic criteria for rUTI and TCM syndrome differentiation, rUTI patients diagnosed with the qi-yin of spleen and kidney deficiency, damp-heat adhesion syndrome by TCM, will be considered as potential participants.

We have taken several methods to ensure recruiting enough participants to reach the target sample size. These methods are shown as follows:
We have counted the outpatient visits of the Nephrology Departments (sub-centers) of these three hospitals over the past three years in advance. And the statistical results showed that the annual outpatient visits of each Nephrology Department in each hospital exceed 60,000 per year. Therefore, each sub-center has enough rUTI patients to support the progress of this study.In order to recruit enough suitable subjects in time, we put recruitment advertisements in all three sub-centers.In order to avoid case shedding during observation and follow-up, we have special investigators responsible for contacting the subjects regularly and reminding and helping them to complete the detection and follow-up on time.

### Consent procedures

Investigators in each sub-center will be responsible for performing and obtaining consent before any conduct of the study. All participants will have consented to randomization and trial participation. The consent process will include a clear explanation of the purpose of the trial, possible benefits and risks, alternative treatment options, and subjects' rights and obligations in accordance with the provisions of the Declaration of Helsinki. All participants will have 24 h to decide whether or not to join in. And participants who are willing to be approached will be allocated randomized after signing written informed consent. The informed consent will be held at each test site on a temporary basis, subject to periodic review by the Data Monitoring Committee (DMC), and be archived.

The original version of the informed consent document is provided as a supplemental file. (Additional file 4)

### Study criteria

#### Diagnostic criteria

##### For UTI

According to *Recurrent Uncomplicated Urinary Tract Infections in Women: AUA/CUA/SUFU Guideline* [1] and *Laboratory Diagnosis of Urinary Tract Infections* [19], patients would be diagnosed with UTI if:
≥10^5^colony-forming units (cfu)/ml bacteria in a clean-catch specimen (urine that had already stay in the bladder for more than 4–6 h);White blood cell (WBC)>10/HP in urinary sediment, or with clinically symptoms of UTI; UTI can be diagnosed according to (1) and (2). If without (2), UTI diagnosis should not be confirmed until the quantitative urine culture rechecked is still ≥10^5^cfu/ml, and the bacteria are the same strain as the former test. Or can be diagnosed if the laboratory test show one of the following:Culture positive for bacteria in the examination of urine in the bladder (bacteria of any quantity is considered);Gram stain of a centrifuged urine specimen can be used for urine sample which is unavailable to do quantitative urine culture. With clinical symptoms, diagnosis can be confirmed if the bacteria more than 1 per oil immersion field; andUrine sample should be reexamined if its colony count≥10^4^cfu/ml but<10^5^cfu/ml, and UTI diagnosis ought to be based on clinical symptoms or examination of urine in the bladder if its colony count does not change.

##### For rUTI

UTI is considered recurrent if with more than 2 episodes in the last 6 months or more than 3 episodes in the last 12 months [1].

#### TCM syndrome differentiation

rUTI Patients will be diagnosed with the qi-yin of spleen and kidney deficiency and damp-heat adhesion syndrome by TCM if they have at least one primary symptom and more than two secondary symptoms or two primary symptoms listed below [20].

#### Primary signs and symptoms

Repeated episodes of dysuria, frequency, and urgency, particularly more severe after fatigueWeakness or pain in the waist and knees

#### Secondary signs and symptoms

Feverish palms and solesXerocheiliaSpontaneous or night sweatingRed tongue with less coating, thready and fast or deep and weak pulse

#### Inclusion/exclusion criteria

Patients will be eligible for the trial if they meet all of the following criteria:
In line with diagnostic criteria for rUTI stated aboveMeet the diagnostic criteria of TCM syndrome differentiation stated aboveAge 18 to 70 yearsAgree to take part in the trial and sign an informed consent

Patients will be ineligible if they have any of the following criteria:
New-onset acute urinary tract infectionIn-dwelling catheterKnown structural or functional urological abnormalities, such as urinary tract congenital malformation, renal pelvis calculi, or other lesionsUrethral syndromeChronic kidney disease (CKD) stage IV-V (eGFR<30 ml/min)Combine with serious heart and liver function damage or diabetes and other diseases which need immediate treatmentAllergic to two or more kinds of antibiotics of this studyPregnancy or lactation (women of childbearing age is demanded to have a urine HCG test)Severe central nervous system diseaseBe participating in other drug clinical trials or have participated in other clinical trials in the last 3 months

#### Participant withdrawal criteria

Participant will withdraw or be rejected for further participation if:
Voluntarily quittingPoor adherenceAny violation of the inclusion criteriaAllergic to two or more of the originally intended drugs or have other specific and intolerable adverse reactionsDrop-out or loss of follow-up during observationLater examination finds other serious diseases (serious heart and liver function damage, blood disease, etc.) or special physiological changes (pregnancy, etc.) and not fit to continue the study

The reasons for the excluded cases will be explained, and the case report form will be kept for future reference. Anyone withdrawn within two weeks after receiving treatment will not be included in the per-protocol population and analyzed as missing data.

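### The withdrawal rule ends trial participation, not just study treatment, and provides no recurrence follow-up for removed patients, so the promised ITT analysis must impute outcomes that could have been collected

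*Protocol article*

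**What the plan says.** All references are to the protocol article.

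- **Participant withdrawal criteria.** The section begins "Participant will withdraw or be rejected for further participation if". Besides voluntary withdrawal and loss to follow-up, the grounds include poor adherence, violation of an inclusion criterion, allergy or intolerable reactions, and serious disease found later. It adds: "Anyone withdrawn within two weeks after receiving treatment will not be included in the per-protocol population and analyzed as missing data".
- **Data analysis.** "ITT will be applied to the full analysis set (FAS) consisting of all randomized subjects". On missing values: "Multiple imputation will be applied to missing data, and sensitivity analysis will be conducted to demonstrate the robustness of the results", with a condition that the proportion of missing data be high. No threshold is given.
- **Primary efficacy outcome.** "The primary efficacy outcome will be the recurrence rate at the 12th week of the follow-up period". Under Trial design, this follows a 12-week treatment period, so it falls at week 24.
- **Retention measures** (Screening and recruitment of participants; Items to be measured and the time points of data collection). Designated investigators contact subjects regularly and help them to complete tests and follow-up. Neither section mentions patients who have been removed.

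**The concern.** The rule treats stopping study treatment and leaving the trial as one event. A patient removed in week 6 for poor adherence or an intolerable reaction has no week-24 recurrence status unless someone goes on collecting it, and the article does not provide for that. The patient still belongs to the ITT set, so the outcome must be imputed.

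Adherence and tolerability arise after randomisation and may be related to both treatment and recurrence. Imputation that takes removed patients to resemble retained patients with the same recorded characteristics is least convincing for this group. An analysis plan can choose a better model or add scenarios, but it cannot recover outcomes that were never collected. At stake is how far the comparison on the primary outcome rests on randomisation and how far on modelling.

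**Working it through.** **1. The passages side by side**

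| Question | Protocol text | Consequence |
|---|---|---|
| What ends when a criterion is met? | Further participation (Participant withdrawal criteria) | Trial follow-up as well as treatment |
| When is the primary outcome read? | Week 12 of follow-up (Primary efficacy outcome) | After any removal during treatment |
| Who is in the ITT analysis? | All randomised subjects (Data analysis) | Removed patients are included |
| Where does their outcome come from? | No follow-up provision; multiple imputation (Data analysis) | Modelled, not observed |

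Only withdrawals within two weeks of treatment are expressly called missing. For later removals, the loss is inferred from the end of participation and the absence of any follow-up provision.

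**2. The plan's own sample size**

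Inputs from Sample size: "The proportion in the treatment group is assumed to be 0.91, and the proportion in the control group is 0.73"; 90% power; "The significance level of the test is 0.025". Sidedness is not stated. One-sided 0.025 corresponds to the two-sided 0.05 in Data analysis.

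n = [p1(1−p1) + p2(1−p2)] × ((z_alpha + z_power)/(p1−p2))²

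= [0.0819 + 0.1971] × ((1.960 + 1.2816)/0.18)² = 0.279 × 324.3 = 90.5, so 91 per group.

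The stated 91 is reproduced. Allowing for 10% attrition gives 91/0.90 = 101.1, or 102 per group and 204 in all, close to the stated 200. There is no sample-size error on this point.

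**3. How far missing outcomes could move the result**

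Assumptions: a fraction d is missing in each arm. The design proportions, 0.91 and 0.73, hold among those observed and are read as success rates, because the documents give no recurrence rate. Let q_T and q_C be the unknown success rates among missing patients. Then

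D = (1−d) × (0.91 − 0.73) + d × (q_T − q_C)

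The extremes are q_T = 0, q_C = 1 (lower) and q_T = 1, q_C = 0 (upper):

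| d in each arm | (1−d) × 0.18 | Lower | Upper |
|---|---|---|---|
| 10% (protocol's attrition figure) | 0.162 | 0.062 | 0.262 |
| 15% (assumed) | 0.153 | 0.003 | 0.303 |
| 20% (assumed) | 0.144 | −0.056 | 0.344 |

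These are logical limits, not expected results. If missing patients did equally well in both arms, D at 10% would be 0.162. If they kept the observed difference, it would be 0.162 + 0.1 × 0.18 = 0.18. The 10% also covers every kind of loss, and the protocol does not say what share would come from the removal rule.

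**4. What follow-up would gain**

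With the pooled two-proportion test at two-sided 0.05, power is 88.8% with 90 per arm (after 10% loss) and 91.8% with all 100. The gain in power is small. The main gain is less reliance on imputation.

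**The case against.** **Imputation and sensitivity analysis are planned, and this is a condensed article.** Both are true. Multiple imputation reduces bias to the extent that recorded characteristics explain removal, and the choice of model and scenarios belongs in an analysis plan. The article nevertheless states the removal rule itself, and that rule ends participation. No imputation model or unseen plan supplies the outcomes that the rule, followed as written, gives up.

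**A reader might infer that the four-times-daily granule causes more removals in the TLF arm and so biases the result.** The documents do not support this. Under Control group, placebo plus CLAT has the same dosage and administration as the treatment group, and Blinding describes a double-blind trial with matching packages. An imbalance could come from tolerability or perceived effect, but the protocol gives no figure. One could assume no true effect, 27% recurrence in both arms, 15% v 5% removal and 50% recurrence among those removed. Completers would then show (0.27 − 0.075)/0.85 = 22.9% v (0.27 − 0.025)/0.95 = 25.8%, a false benefit of 2.8 points. Those removal and recurrence rates have no source, and a completers-only comparison is not the planned ITT analysis. With equal removal and equal recurrence among those removed, the false difference is zero.

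**A reader might infer that UTIs already seen are thrown away.** The missing-data sentence covers only withdrawals within two weeks, is tied to the per-protocol population and is loosely worded. Other sections point the other way. Treatment of acute-onset UTI during the treatment period has such cases marked as no recovery, and Statistics of recurrence counts from treatment to the end of follow-up. What stands is an ambiguity: a patient with a UTI in week 1 who is then withdrawn falls under both rules.

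**Informative missingness is an inference.** This is correct. It is plausible for non-adherence and intolerance, and less clear for an inclusion violation, which is a matter of baseline status.

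**Conclusion.** The point holds as a gap between the removal rule and the ITT promise. As written, patients removed for poor adherence, an inclusion violation, intolerable reactions or later serious disease leave the trial before the primary outcome is read, and no section keeps them in follow-up. Their outcomes would have to be imputed, for reasons that may be related to recurrence.

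Neither the direction nor the size of any bias can be established from the documents. The only size offered is a bound: with 10% missing in each arm and 0.91 v 0.73 among those observed, the all-randomised difference lies between 0.062 and 0.262. At that attrition even the worst case keeps the point estimate above zero; at an assumed 20% it does not. The bound takes the design proportions as the observed success rates and covers all attrition, not only removal under this rule. The protocol should be changed, since the change is cheap and imputation cannot stand in for it.

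**What to change.** 1. In Participant withdrawal criteria, leave the reasons for stopping study treatment unchanged. Add that a patient who meets one of them stays in the trial and is followed for recurrence to the end of follow-up (week 24), using the visits and telephone contacts already planned, unless the patient withdraws consent for follow-up.
2. Clarify that the missing-data sentence in that section does not override a UTI already observed, and that such events count in the ITT analysis. This brings it into line with Treatment of acute-onset UTI during the treatment period and Statistics of recurrence.
3. Leave the choice of sensitivity scenario for outcomes that remain missing to the analysis plan.

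The cost is a protocol wording change and a few more follow-up contacts by investigators already assigned to that work.
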